**Figure 3. F3:**
[figure not shown]
Images of the outdoor space at the conventional Early Learning and Child Care programs (ie, usual care sites).

A priori power analysis was conducted using G*Power (Heinrich-Heine-Universität Düsseldorf) to estimate the sample size required to detect meaningful group differences over time for the primary objective of the study (ie, child outcomes). Given the complexity of general linear mixed-effects models and the limited availability of accessible power calculation tools for these models, a repeated-measures ANOVA with a within-between interaction was used as an approximation. This approach allows for estimating power to detect changes within participants over 3 time points and differences between 2 groups (experimental vs usual care). The calculation assumed a small effect size (*f*=0.20), a power of 0.80, and an alpha level of .05. This choice aligns with findings from systematic reviews indicating that ELCC interventions often yield small but statistically significant effects on children’s development [24]. Based on these parameters, the estimated required sample size is 42 child participants (21 per group). While our primary analyses use general linear mixed-effects models, this conservative ANOVA-based estimate provides a reasonable benchmark for planning purposes and may underestimate statistical power. Given the open cohort design, in which participants may enter and exit over time and contribute varying numbers of observations, precise specification of variance and correlation parameters is challenging at the design stage. In the absence of prior data, assumptions were therefore based on conservative estimates. To further strengthen these estimates, an internal pilot approach will be used whereby preliminary data from the first year of the study (ie, Wave 1: T0, T1, and T2) will be used to estimate key parameters (eg, variance components and within-subject correlation). These estimates will inform a refined assessment of sample size and statistical power for the remaining study period. This process will not involve formal hypothesis testing and will not affect the integrity of the primary analyses. The current sample size estimation is treated as a minimum threshold. In practice, we aim to enroll 100% of children attending the outdoor-focused ELCC center (ie, experimental site) and seek to match this number across the usual care sites. Therefore, we anticipate a substantially larger sample size that will improve the precision and generalizability of our findings [25].

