#### Executive Functioning

Two tasks from the NIH Early Years Toolbox are used to assess visual-spatial working memory ([name]) and task inhibition (Go/No-Go). These tasks were developed as brief, playful assessments administered using an iPad to examine young children’s cognitive development. The [name] task assesses visual-spatial working memory. The Go/No-Go tasks assess a child’s inhibition. For more information on these assessments, see Early Years Toolbox [44]. These assessments have been previously validated in children aged 2.5‐5 years old and demonstrate very good reliability, convergent validity, and sensitivity [45,46]. Executive functioning tasks are completed by children aged 36 months and older in this study.

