## Discussion

### Study Significance

The SPROUT study is the first in Canada, and to our knowledge globally, to directly and longitudinally compare a licensed outdoor-focused ELCC program with conventional ELCC programs. This research addresses a significant gap in the current evidence base regarding the short- and long-term developmental and health impacts of outdoor-focused ELCC models. By using a robust and appropriately powered design, the SPROUT study provides a unique opportunity to examine whether and how outdoor-focused ELCC models influence not only child health, development, and well-being, but also caregiver beliefs and attitudes, and the well-being, job satisfaction, and continued professional development of educators.

Importantly, the SPROUT study explores how outdoor-focused programs affect educators’ knowledge and attitudes toward outdoor play. These insights may support strategies to retain and strengthen the early childhood education workforce, a major challenge and need in Canada, given the new Canada-wide Early Learning and Child Care Act, which commits to adding 250,000 new licensed ELCC spaces in Canada by March 2026 [64]. The study also examines caregiver attitudes and support behaviors toward outdoor play, offering valuable information on how these beliefs evolve over time and differ across program types. This knowledge will serve to expand on the growing body of work being done in Canada exploring caregiver and educator perspectives of outdoor play and learning and how to support change toward promoting more outdoor play opportunities for all children [11,65]. Together, this body of literature may help inform strategies to promote outdoor play in ELCC, at home, and in community spaces.

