### Strengths and Limitations

This study has several notable strengths. The longitudinal cohort design enables temporal comparisons between outdoor-focused and conventional ELCC programs, providing insight into developmental changes over time. The study is appropriately powered, and the use of a naturalistic cohort design adds rigor and ecological validity. A comprehensive set of valid and reliable child outcome assessments, including both direct measures and caregiver-reported tools, ensures robust data collection. Additionally, this study examines changes in educator well-being, an area that has received little attention in outdoor-focused ELCC programs.

Despite this study’s strengths, there are limitations that we anticipate having a potential impact on the findings. Due to the naturalistic design of this study, randomization is not possible, which may influence causal inferences. Families self-enroll in the outdoor-focused program, introducing the potential for selection bias. However, both the experimental and usual care sites are funded through the Canada-wide Early Learning and Childcare program, where caregivers put their name on a city-wide waitlist and typically accept whatever program has capacity. Similarly, educators also self-select and apply to work at the center of their choice, and the outdoor-focused ELCC prioritizes educators who have training in outdoor-focused childcare, introducing a possible selection bias. To address this, we will explore baseline differences and focus our analyses on differences in change over time, inherently accounting for individual differences. Accessibility is also limited, as the outdoor-focused center is located outside the city center and is not yet reachable by public transit, potentially leading to a less diverse sample. Selection bias is likely, as families participating in the SPROUT and/or SPROUT-able studies may have an interest in child development, movement behaviors, and/or outdoor play, which could influence study outcomes. Finally, while a strength of this study is the intentional inclusion of children with disabilities, the study remains limited by a lack of valid and reliable measures of child development and health for diverse disability types.

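### The 42-child calculation is justified by small effects, but f = 0.20 here means a group difference in change of about 0.85 to 0.98 SD, so the small-effect and conservative labels and the power claims are not supported

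*Protocol article*

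**What the plan says.** The power paragraph (Methods, Participants and Settings) concerns the primary objective, child outcomes. As a stand-in for the mixed model, "a repeated-measures ANOVA with a within-between interaction was used as an approximation", covering "changes within participants over 3 time points and differences between 2 groups (experimental vs usual care"). On effect size: "The calculation assumed a small effect size (*f*=0.20"), with power 0.80 and alpha .05. The choice is tied to reviews that find small effects of early learning interventions. The result: "Based on these parameters, the estimated required sample size is 42 child participants (21 per group").

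No within-child correlation or sphericity value is given. The text adds that "this conservative ANOVA-based estimate provides a reasonable benchmark for planning purposes and may underestimate statistical power". It treats 42 as a floor, expects a substantially larger sample, and plans to use first-year data to estimate variance components and correlation and to refine the power assessment.

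The Data Analysis Plan defines the intervention effect through the group-by-time interaction, as a difference in change from baseline. The Discussion states adequate power as fact: "By using a robust and appropriately powered design" (Study Significance, in a sentence that goes on to caregiver and educator outcomes) and "The study is appropriately powered, and the use of a naturalistic cohort design adds rigor and ecological validity" (Strengths and Limitations).

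**The concern.** Cohen's f for an interaction is not on the scale on which most readers judge an effect. An f of 0.20 looks modest, but the study tests differences in change, and on that scale the same f may be large. If so, the stated reason for the sample size (effects in this field are small) and the sample size itself do not belong together, and calling the estimate conservative points the reader the wrong way. At stake is the reading of a non-significant group-by-time result: a study described in advance as appropriately powered invites the conclusion that no worthwhile effect exists.

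**Working it through.** **Inputs.** From the power paragraph: k = 2 groups, m = 3 occasions, f = 0.20, power 0.80, alpha 0.05, N = 42. From Results: 110 children enrolled (67 experimental, 43 usual care), of whom 39 and 23 have all three Wave 1 assessments. (The Abstract gives 86 dyads with the same 67 and 43, and 43 and 27 completers; the Results figures are used here.) Assumed, because not stated: within-child correlation ρ, shown over a range, and sphericity ε = 1.

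**1. Reproduce 42.** Noncentral F with λ = f²·N·m/(1−ρ), df1 = (k−1)(m−1) = 2, df2 = (N−k)(m−1).
- N = 42, ρ = 0.5: λ = 0.04 × 42 × 3 / 0.5 = 10.08, df2 = 80, power 0.803.
- N = 40: power 0.782.

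So 42 is correct under these settings. It depends on them:
- ρ = 0.3, 0.4, 0.6, 0.8 gives N = 58, 50, 34, 18. Under sphericity, ρ = 0.48 already gives 44 and 0.55 gives 38, so about 0.5 was used.
- ε = 0.9 or 0.75 (at ρ = 0.5) gives N = 46 or 52.
- Two other definitions of f that the software offers give 122 and 124, so the definition used in step 2 is the one behind 42.

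**2. What f = 0.20 means as a difference in change.** Let d_t be the group difference at occasion t in units of the outcome SD. For two equal groups, f = SD(d_t)/2, with the SD taken over the three occasions (divisor 3). This does not involve ρ.
- Linear divergence, d = (0, D/2, D): f = D/√24, so D = 0.20 × 4.899 = 0.98.
- Step, d = (0, D, D): f = D/√18, so D = 0.20 × 4.243 = 0.85.

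For any other three-point shape, the largest change in the group difference lies between these two values. Simulated power at 21 per group and ρ = 0.5 is 0.81 for both patterns.

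**3. Detectable difference at 80% power.** Solve for λ (10.005 at N = 42; 9.77 at N = 110), then Σ(d_t − d̄)² = λ(1−ρ)·N/(n₁n₂). This sum equals D²/2 for the linear and 2D²/3 for the step pattern.
- 21 and 21, ρ = 0.5: 10.005 × 0.5 × 42/441 = 0.476, so D = √(2 × 0.476) = 0.98 and √(1.5 × 0.476) = 0.85.
- 67 and 43, ρ = 0.5: 9.77 × 0.5 × 110/2881 = 0.1865, so D = 0.61 and 0.53.

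| Children (three assessments each) | ρ = 0.3 | ρ = 0.5 | ρ = 0.7 | ρ = 0.8 |
|---|---|---|---|---|
| 21 and 21 | 1.00–1.16 | 0.85–0.98 | 0.65–0.76 | 0.54–0.62 |
| 39 and 23 | 0.85–0.98 | 0.72–0.83 | 0.55–0.64 | 0.45–0.52 |
| 67 and 43 | 0.63–0.72 | 0.53–0.61 | 0.41–0.47 | 0.33–0.39 |

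Entries are in SD units, step to linear, with no centre-level variance.

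Cross-check with a single T0–T2 change comparison at ρ = 0.5: the SD of change is √(2 × 0.5) = 1, and 2.80 × √(1/21 + 1/21) = 0.87. For 67 and 43, 2.80 × √(1/67 + 1/43) = 0.55.

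**4. Power for smaller differences at N = 42, ρ = 0.5 (linear to step).** 0.2 SD: 8–9%. 0.4 SD: 19–24%. 0.5 SD: 28–36%.

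**The case against.** **The study is not run at 42.** This stands. The article calls 42 a minimum, and 110 children are enrolled after one year of three. With 67 and 43, power for f = 0.20 is 0.996 at ρ = 0.5. For an effect half that size, f = 0.10 (0.42–0.49 SD of change), it is 0.60 at ρ = 0.5 and 0.83 at ρ = 0.7. The unequal split costs only about 5% (effective N = 4 × 67 × 43/110 = 104.8). A reader might infer that the study has little chance of finding moderate differences; the enrolled numbers do not support that.

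**The correlation is unknown and a remedy is planned.** This also stands in part: the detectable difference shrinks at high correlation, and the Wave 1 internal pilot will estimate it. But step 2 is independent of the correlation, and the pilot as described does not revisit what f = 0.20 means. The Discussion claims adequate power without waiting for it.

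**The mixed model may do better than the ANOVA.** Covariates, partial records and up to six follow-ups could add power, so the remark that power may be understated is possible. It does not make the estimate conservative: sphericity is the most favourable value, and attrition and centre differences are left out.

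**Confidence intervals are already promised.** True (Data Analysis Plan), which lessens the risk of misreading a null result.

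Two further inferences should be resisted. The article says "Executive functioning tasks are completed by children aged 36 months and older in this study", and the peg, timed up-and-go and grip tests share that limit. But power computed from the children who were old enough at entry would ignore those who reach 36 months during follow-up. Likewise, power computed from the 28 enrolled educators less the 6 who left would ignore continuous recruitment.

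**Conclusion.** The point holds as a fault of interpretation, not of arithmetic. Forty-two is the right answer for f = 0.20 under unstated, mostly favourable assumptions, but f = 0.20 is a difference in change of about 0.85 to 0.98 SD and cannot be justified by an expectation of small effects. The word conservative is unsupported. That the study is appropriately powered is not shown for small effects, even with all 110 children: about 0.53 to 0.61 SD is detectable at correlation 0.5 and 0.41 to 0.47 SD at 0.7. Those figures assume three assessments per child and no centre-level variance; a centre effect would make them worse. The Study Significance sentence also links the power claim to caregiver and educator outcomes, which the calculation does not cover. The documents do not show that enrolment is inadequate or that the analysis must change.

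**What to change.** Change the text only; enrolment and analysis stay as they are.

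- State the assumed within-child correlation, the sphericity value and the definition of f used.
- Express the target as a group difference in change in SD units, with a range over plausible correlations.
- Report the minimum detectable difference for the enrolled 67 and 43, and update it with the Wave 1 internal pilot estimates.
- Drop *small* as the description of f = 0.20, and drop *conservative*.
- In Study Significance and in Strengths and Limitations, limit the statement of adequate power to child outcomes and to differences of at least the reported size.

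The cost is a few sentences and a stated power that looks less favourable.

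### The internal pilot re-estimates variance and correlation, but the plan's only target effect is a standardised f=0.20, so a re-assessment on that target would be falsely reassuring

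*Protocol article*

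**What the plan says.** All of this stands in the power paragraph of Methods, Participants and Settings.

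- Planning test: "a repeated-measures ANOVA with a within-between interaction was used as an approximation", covering "changes within participants over 3 time points and differences between 2 groups (experimental vs usual care".
- Inputs: "The calculation assumed a small effect size (*f*=0.20), a power of 0.80, and an alpha level of .05".
- Result: "the estimated required sample size is 42 child participants (21 per group". This number is described as a floor. The team aims to enrol every child at the outdoor-focused center and to match that number at usual care.
- Correlation, sphericity, raw SD and a difference in score units are not given. The article says that "precise specification of variance and correlation parameters is challenging at the design stage" and "In the absence of prior data, assumptions were therefore based on conservative estimates".
- Internal pilot: Wave 1 data (T0, T1, T2) "will be used to estimate key parameters (eg, variance components and within-subject correlation". Then: "These estimates will inform a refined assessment of sample size and statistical power for the remaining study period".

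Elsewhere, the Data Analysis Plan lists child age among the example covariates of the mixed models and includes a random effect per child. Results reports 110 children enrolled, 67 experimental and 43 usual care.

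**The concern.** An internal pilot corrects a sample size by replacing a guessed SD with an observed one while the target difference stays fixed in score units: a larger SD then gives a larger N. Here the only stated target has already been divided by the SD. Whatever variance Wave 1 shows, it cannot change N through f. N can still respond to the correlation and to sphericity, but f=0.20 stands for so large a difference in change that hardly any result would raise doubt at current enrolment.

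What is at stake is the meaning of the power statement. The Discussion already describes the study as appropriately powered. A re-assessment reporting near-certain power would seem to confirm this, would weaken the case for closing the gap between 43 and 67 children, and would lend null results more weight than they deserve.

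**Working it through.** **1. Reproducing 42.** From the article: f=0.20, m=3 occasions, k=2 groups, alpha .05, power 0.80. Assumed, because not stated: correlation rho=0.5 and sphericity epsilon=1.

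λ = f²·N·m·ε/(1−ρ), with df1 = (k−1)(m−1)ε and df2 = (N−k)(m−1)ε.

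At N=42: λ = 0.04×42×3/0.5 = 10.08, df = (2, 80), power 0.803. At N=40: power 0.782. So 42 reproduces with these two values.

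**2. The variance cancels.** Write the effect in raw units as f×SD. Then λ = (0.20·SD)²·42·3/(SD²·0.5), which is 10.08 for an SD of 5, 10 or 20.

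**3. What still moves N at f=0.20.**

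| Change from ρ=0.5, ε=1, m=3 | N |
|---|---|
| ρ = 0.3 | 58 |
| ρ = 0.7 | 26 |
| ρ = 0.8 | 18 |
| ε = 0.75 | 52 |
| ε = 0.5 | 68 |

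**4. The check at current enrolment.** N=110, same formula, which assumes equal groups:

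- ρ=0: λ = 0.04×110×3 = 13.2, power 0.91
- ρ=0.3: λ = 18.9, power 0.98
- ρ=0.5: λ = 26.4, power above 0.99
- ρ=0.5, ε=0.5: power 0.95
- ρ=0, ε=0.5: power 0.72, the only one of these cases below 0.80

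The 67/43 split lowers the effective N to 4×67×43/110 = 104.8, a small change.

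**5. What f=0.20 means.** In this form f² is the mean squared interaction effect over the six cells, divided by the single-occasion variance.

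- Linear divergence: cell effects ±(−a, 0, a), so f = a√(2/3) and a = 0.245. The group difference in T0–T2 change is 4a = 0.98 SD.
- Step after baseline: cell effects ±(−2b, b, b), so f = b√2 and b = 0.141. The difference in change is 6b = 0.85 SD.

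**6. Power for smaller differences in 12-month change.** Assumptions: 67 vs 43 children, two-sided .05, t test with 108 df, no loss, no clustering. SE = √[2(1−ρ)(1/67+1/43)] in single-occasion SD units.

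| ρ (assumed) | SE | Power, 0.2 SD | Power, 0.3 SD | Detectable at 80% power |
|---|---|---|---|---|
| 0.5 | 0.195 | 17% | 33% | 0.55 SD |
| 0.7 | 0.151 | 26% | 50% | 0.43 SD |

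The last column is (1.98 + 0.845)×SE.

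**7. The role of age.** Table 2 gives an age SD of 10.9 months. Suppose the same-age correlation is 0.5 and age explains a share R² of the raw variance (both assumed). The raw correlation is then 1−0.5(1−R²), that is 0.60, 0.70 or 0.80 for R² of 0.2, 0.4 or 0.6. With f=0.20 kept on the raw SD, N falls to 34, 26 or 18. For an effect of f=0.20 on the same-age SD, the true power at those N is 0.705, 0.573 or 0.409.

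A simulation with age SD 10.9 months, true same-age correlation 0.5 and growth of 0.05, 0.1 or 0.2 same-age SD per month agrees. Without age in the model the correlation was 0.61, 0.77 and 0.91; with baseline age in the model it was 0.48, 0.49 and 0.52. The interaction SE stayed at 0.044 to 0.046 throughout, so the added correlation buys no precision.

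**The case against.** - **The article never says that f=0.20 is carried into the re-assessment.** This is correct. The ANOVA is called an approximation, and variance components are mixed-model vocabulary, so the re-assessment may be meant for the planned model. But no other target is stated, and the text describes strengthening the variance and correlation assumptions, not replacing the effect.
- **Age is in the planned model.** This stands and limits the point. A reader might infer that the wide age range necessarily inflates the correlation and that refined power will therefore be overstated. The documents do not support that. Age adjustment removed the inflation in simulation, and age-standardised scores would avoid it. Several tests are given only from 36 months, which narrows the age range. The article does not say which estimates the pilot will use.
- **The correlation is not the only driver.** This also stands. Sphericity and the number of occasions move N, a correlation below 0.5 raises it, and variance components are not idle because the correlation is their ratio.
- **42 is a floor.** A reader might infer that the step would shrink the study. It would not: full enrolment at one center and matching at the others is a separate aim.
- **The 17 to 50% figures concern the choice of f.** They do. They belong here because a re-assessment on f=0.20 could not bring that problem to light.
- **A journal article condenses.** It does, but this one states both the target and the parameters to be re-estimated, and the two do not fit together.

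**Conclusion.** The point holds in conditional form. If the re-assessment keeps the plan's only stated target, the raw variance has no influence on N. The check also passes at 110 children for almost any correlation, whether or not age is adjusted for. At the same enrolment, power is about 17 to 26% for a 0.2 SD group difference in 12-month change and about 33 to 50% for 0.3 SD.

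These last figures rest on an assumed correlation of 0.5 to 0.7, with no loss and no clustering; the documents give no outcome SD or correlation. The arithmetic on f=0.20 rests on the G*Power form that reproduces 42. A further overstatement from age is possible only if the correlation comes from raw scores without age adjustment. The consequence is a power statement that reassures without testing the design.

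**What to change.** For the re-assessment, replace f=0.20 with a target group difference in 12-month change, in score or age-standardised units, for the main child outcome or outcomes. Take the SD of change and the within-child correlation from Wave 1, conditional on age and pooled within group. Report power and the detectable difference at the numbers the four centers can supply. If a target other than f=0.20 is already intended, state it in the power paragraph.

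The cost is a recalculation on data already collected, a few lines of text, and a less favourable stated power. No new data are needed.
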